**Figure 1 F1:**
[figure not shown]
**Flow diagram according to the trial protocol**.

The outcomes to be studied will be preterm delivery < 34 and < 32 weeks of gestation and associated morbidity and mortality: early neonatal sepsis, bronchopulmonary dysplasia, periventricular leukomalacia, necrotizing enterocolitis, and prematurity-related retinopathy. Definitions of these conditions are similar to those used by the Vermont-Oxford Network, published in 2002.

A more detailed account of selected procedures and definitions is presented below.

### 3.2. Laboratory Methods

#### Measurement of vaginal pH

Vaginal pH will be measured by a strip with discrimination of 0.5, to evaluate women with pH higher than or equal to 4.5 and higher than or equal to 5.

#### Collection of clinical specimen for bacteriological analysis

Nugent Method - A swab will be used to obtain a cervicovaginal smear that will be Gram stained to be examined and interpreted according to the criteria described by Nugent, Krohn and Hillier [16]. A complementary analysis of the vaginal smear will be performed (400 × magnification, phase contrast microscope): the determination of the number of leukocytes per epithelial cell and the proportion of parabasal epitheliocytes to allow for the detection of moderate and severe aerobic vaginitis [64].

#### Quantitative tests of cervicovaginal cytokines

Cervicovaginal fluid will be collected by using 2 Dracon swabs (Fisherland, Fisher Scientific, Pittsburgh, PA, USA). Each swab will be placed in the vagina and cervical os for 10 seconds, thus reaching saturation. Next, each of them will be placed in a polypropylene plastic tube containing tampon-saline phosphate (PBS). The material will be stored at -20C. The quantification of the selected inflammatory cytokines (IL-1beta, IL-1ra, IL-6, IL-8 and IL-10) will be conducted by an immunoenzymatic test of capture or "sandwich-type" test, using R & D Systems, or, if possible, a special LUMINEX platform in order to broaden the spectrum of cytokines to be analyzed.

#### Genetic polymorphisms detection

A swab of the oral mucosa will be obtained and the DNA will be extracted by the conventional procedure [64]. Relevant single nucleotide polymorphisms will be investigated for TNF, IL-1beta, IL-1ra, IL-6 e IL-10. They will be genotyped with the PCR and sequence specific primers (PCR-SSP).

### 3. 3. Criteria to Diagnose Neonatal Morbidity

The criteria used to identify study morbidty were adapted from those defined by the Vermont Oxford Network in 2002.

- Early neonatal sepsis (72 h) - blood for the leukogram should be obtained during the first 72 hours; diagnosis will be reached by analyzing the neutrophilic index (ratio between immature neutrophils/total neutrophils). Diagnosis will also be done in case of positive hemoculture.

- Periventricular leukomalacia -evaluation will be conducted in newborns less than 32 weeks' gestation by performing a transfontanel ultrasound. To be considered cystic periventricular leukomalacia, multiple small periventricular cysts *must *be identified.

- Bronchopulmonary dysplasia - evaluation should be conducted in newborns less than 32 weeks' gestation, using the criteria of a) suggestive X-Ray and b) newborn need of any supplemental oxygen on the date of week 36, gestational age.

- Necrotizing enterocolitis - evaluation should be conducted in newborns with less than 34 weeks, using both clinical and radiographic criteria.

- Newborn retinopathy - evaluation will be conducted by a neonatologist trained in performing indirect ophthalmoscopy in newborns. The exam will be realized at 4 weeks after birth in newborns less than 1500 g.

### 3.4. Sample size

The estimation of the sample was based on the following information:

a) international and national data (very scarce) on the incidence of, and microorganisms associated with bacterial vaginosis and intermediate degree infection in pregnant women, taking into consideration different concepts and degrees of severity of those conditions and also, different populations and techniques used to identify and evaluate it [21,23,24] as well as the probabilities of natural recovery from vaginosis [10];

b) an estimate of the intersection of intermediate degree/BV scores and pH cutt off point (4.4), i.e., the percentage of pH positive (> 4.4) asymptomatic pregnant women who present a normal (0-3) Nugent score);

c) an estimate of the percentage of spontaneous preterm delivery expected in the placebo group [21,25];

d) an estimate of the effectiveness of probiotics to be tested in the study.

An initial loss, close to 20% of the pregnant women admitted for routine prenatal care, was supposed to occur due to the clinical exclusion criteria. The use of the vaginal pH < 4.5 parameter as a cutoff point to sort the pregnant women in whom the Nugent test will be performed, would bring about the exclusion of around 40% of the pH tested women; it also would imply the loss of one third of the less than 34 week spontaneous preterm deliveries expected to occur in the population that passed the clinical screen, although around 45% of Nugent score of the remaining population (after clinical and pH screens) would fall between 0-6 [25].

On the other hand, for that remaining population, the estimated incidence of BV plus intermediate degree would be 85%, which would result in the exclusion of around 15% of the population that passed the clinical and pH screens [25]. Therefore, the combination of the pH and Nugent criteria was expected to exclude near 50% of the pregnant women who passed the clinical screen; it also would imply the loss of about 20% of the less than 34 week spontaneous preterm deliveries expected to occur in the population that passed the clinical, pH and Nugent screens. The rate of spontaneous preterm deliveries < 34 weeks was estimated to be 6% in the placebo group and close to 3% in the intervention group, i.e., efficacy was supposed to be 50%; for spontaneous preterm deliveries under 32 weeks, the corresponding estimates would be close to half of those percentages.

Based on a significance level of 0.05 and a 80% power to show differences in rates of less than 34 week spontaneous preterm deliveries, the population to be randomized was estimated to be 1500 pregnant women (to show 50% efficacy regarding spontaneous preterm deliveries less than 34 weeks gestation). Taking into consideration the previous losses plus 5% refusals to give written informed consents as well as 15% loss related to adherence to treatment, a sequence of nearly 3500 pregnant women shall be screened in order to obtain the desired sample.

### 3.4. Data analysis

A post randomization table will comprehend the distribution of all relevant variables. Outcomes will be analyzed according to intention to treat and effective treatment. The Student t test, the X2 test for proportions and the Fisher test will be used in the preliminary data analyses. In those cases where the Student test does not apply due to non Gaussian distribution, the Mann-Whitney test will be used. Outcomes will also be analyzed according to subgroups of selected risk factors at admission and categories of severity of the infectious process, according to the study biological markers. The association between knowledge based selected factors and dichotomous or continuous outputs will be investigated under the framework of generalized additive models to handle non linear predictors as well as non Gaussian responses.

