## 1- Introduction (Scientific background and explanation of rationale)

In the United States, where prematurity rates are higher than those in Western Europe, nearly 11% of babies are born premature and preterm delivery is associated to approximately 80% of fetal, neonatal and infants' deaths [1]. Studies in Brazilian urban areas indicate a prematurity rate above 10% - as high as the American rate [2,3].

About 25% to 30% of preterm deliveries occur due to medical indication and the remaining percentage occurs spontaneously [1-4]. Neonatal mortality and morbidity risks are inversely associated to gestational age at birth; spontaneous preterm deliveries that occur before the 35th week of gestation, and particularly before the 32nd week of gestation, have been strongly associated to intrauterine infection. [5,6].

Approximately half of the neurological disabilities found in children, including cerebral palsy, are attributed to prematurity; those disabilities limit the learning capabilities and social abilities during childhood and adult life and imply a significant overload for their families and for society. The subgroup of babies born before the 32nd week of gestation, which corresponds to around 2% of those born alive, represents the largest portion of deaths and neonatal neurological problems [5,6].

The cost of taking care of premature children in developed countries is very high [7]; in developing countries, like Brazil, the problem is composed by a low effectiveness of the assistance provided in nurseries, mainly that rendered in NICUs.

Important risk factors to spontaneous preterm delivery, such as age < 18 years, race, education, and bacterial vaginosis are associated with low social-economic level. The most important factor in spontaneous preterm delivery (SPTD), history of preterm delivery, increases 3 times the risk of a subsequent preterm delivery and is probably associated to underlying risk factors [4,8,9].

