### 3.1. Randomization process

It was stratified for the factor history of preterm delivery (HPD), and blocked by using a permuted block design. Stratified randomization was attained by producing one blocked and randomized list for each stratum. Blocks of size 8 were specified for the strata of non HPD; for the group of HPD, blocks of size 4 have been adopted. The sequence for randomization was electronically generated by an independent research assistant.

Women with a Nugent score between 4 and 10 will be randomized, after a second written informed consent, as soon as possible. Research nurses responsible for allocation are not directly involved with prenatal care, i.e., with clinical screening. Allocation will be concealed by sealing both placebo and intervention capsules, identical in aspect, in sequentially numbered identical containers according to the allocation sequence. Besides the pregnant women, doctors/nurses and researchers/evaluators (assessment of outcomes, including Nugent score and other lab procedures) are to be blinded to the randomization process.

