The trial will test two lactobacilli strains, Lactobacillus rhamnosus GR-1 and Lactobacillus fermentum RC-14, the latter presently denominated Lactobacillus reuteri RC-14, developed and studied by Reid et col [33-36] as earlier mentioned. Each capsule contains an amount superior to one million bacilli of each strain. Each participant will receive, from the research nurse, one box with six bottles, box and bottles equally numbered, of probiotics/placebo, each bottle containing 30 capsules, corresponding to a maximum intervention period of 12 weeks. Participants will be then instructed to maintain the box at the refrigerator (not at the freezer) and to take two capsules per day, along a period that may vary from six to twelve weeks, depending on the participant's gestational age at the moment of enrollment in the study. Enrolled women will be free to contact the research assistant nurses or the research doctor; one week after randomization, they will be contacted by telephone for information about treatment. More detailed questioning will be made at each routine prenatal visit until the completion of the trial (around the 24-25th week of gestation) regarding adhesion/adherence, adverse events and clinical intercorrences, according to a previously designed form. Adherence will be fostered, when appropriate. At the post treatment prenatal care visit, randomized women will be asked to bring back all bottles; capsules remaining in the bottles they return will be counted. Adherence is defined as at least 6 wks of treatment.

At the post-treatment prenatal care visit, vaginal pH will be assessed; cervicovaginal smear and fluid will be collected to determine the post intervention Nugent score and levels of the selected cytokines in order to evaluate changes in those parameters (secondary results).

A detailed and extensive protocol was developed. Standard Operational Procedures were elaborated to cover the logistics and operational aspects of the trial. They cover not only details related to the whole screening process and materials' collection, transportation and storage but also elements that are relevant to the randomization process, including creation and protection of the allocation sequence, labeling of bottles and boxes, as well as the filling in and sending out the Case Record Forms.

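### Randomisation is stratified by history of preterm delivery, but no named test or model carries the stratum into the comparison of arms; the cost is small and the repair is wording

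*Protocol article*

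**What the plan says.** On the design, section 3.1 (Randomization process) says of the allocation: "It was stratified for the factor history of preterm delivery (HPD), and blocked by using a permuted block design". Each stratum has its own list: "Blocks of size 8 were specified for the strata of non HPD; for the group of HPD, blocks of size 4 have been adopted". The Introduction ranks this history as the most important factor in spontaneous preterm delivery and says that it "increases 3 times the risk of a subsequent preterm delivery".

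On the analysis, section 3.4 (Data analysis) applies intention to treat and effective treatment, then states: "The Student t test, the X2 test for proportions and the Fisher test will be used in the preliminary data analyses". Mann-Whitney replaces the t test for non-Gaussian data. Two further analyses follow: "Outcomes will also be analyzed according to subgroups of selected risk factors at admission", and "The association between knowledge based selected factors and dichotomous or continuous outputs will be investigated under the framework of generalized additive models".

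On the markers, section 3.1 collects pH, smear and fluid again after treatment, with the aim "to determine the post intervention Nugent score and levels of the selected cytokines in order to evaluate changes in those parameters". These are labelled secondary results.

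**The concern.** Stratifying the randomisation makes the two arms alike on a strong predictor. An analysis that leaves the predictor out still estimates the effect without bias, but it keeps the between-stratum variation in its standard error although the design has removed it from the comparison. P-values come out a little too large and intervals a little too wide.

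Every test named in section 3.4 that could compare the arms has this form. The additive models are described as examining selected factors, with no mention of the treatment contrast or the stratum. A subgroup analysis by history of preterm delivery, if there were one, would give separate estimates and not a stratified overall test.

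Two smaller points follow. Chi-square and Fisher are both named for proportions without saying which applies to the main outcome, and they differ in power by more than the stratum does. For the secondary markers, change is to be evaluated, but no baseline-adjusted comparison of arms is named.

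**Working it through.** **Inputs.** From section 3.4 (Sample size): spontaneous preterm delivery before 34 weeks in 6% on placebo and about 3% on probiotic, significance level 0.05, power 80%, 1500 women randomised. From the Introduction: threefold risk, stated for any subsequent preterm delivery and applied here to the 34-week outcome. Assumed because the article does not give them: two-sided test, 1:1 allocation, the same relative effect in both strata, stratum prevalence 5% to 30%.

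**1. The plan's own figure.** The uncorrected two-proportion formula per arm is

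n = [1.96·√(2·0.045·0.955) + 0.8416·√(0.06·0.94 + 0.03·0.97)]² / 0.03² = 0.8207² / 0.0009 = 748.4, so 749 per arm and 1498 in total.

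This reproduces 1500, and power at 750 per arm is 80.1%. One-sided (1180), one-sided with continuity correction (1310) and two-sided with continuity correction (1628) do not reproduce it. The sample size thus corresponds to an unstratified chi-square comparison.

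**2. Why leaving out the stratum is conservative.** Take prevalence 20% and no treatment effect. The lower stratum risk is 0.06 / (0.8 + 3·0.2) = 0.0429 and the higher is 0.1286. The variance that the unstratified test assumes per woman is 0.06·0.94 = 0.0564. The between-stratum part is 0.2·0.8·(0.1286 − 0.0429)² = 0.0012, leaving 0.0552 within strata. The ratio is 0.979. The effective critical value is 1.96/√0.979 = 1.981, which gives a type I error of about 0.048.

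**3. Simulation.** 200,000 trials per setting, 1500 women, exactly balanced within stratum. Pearson chi-square is compared with the Cochran-Mantel-Haenszel (CMH) test, whose variance sums n²·m(N−m)/[N²(N−1)] over strata (n per arm, m events and N women in the stratum).

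| Prevalence | Power, chi-square | Power, CMH | Type I error, chi-square | Type I error, CMH |
|---|---|---|---|---|
| 5% | 0.810 | 0.813 | 0.048 | 0.050 |
| 10% | 0.812 | 0.816 | 0.047 | 0.050 |
| 20% | 0.813 | 0.817 | 0.047 | 0.050 |
| 30% | 0.811 | 0.815 | 0.048 | 0.050 |

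With a sixfold risk, as a stress case, power is 0.815–0.816 against 0.825–0.828, a loss of about 1.0 to 1.2 points. Type I error is then 0.041–0.044 for chi-square.

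**4. Chi-square or Fisher.** Exact enumeration at 750 per arm, 6% against 3%, gives power of 81.0% for chi-square and 77.3% for Fisher. Under a common rate of 4.5%, the true size is 0.050 and 0.037.

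**5. Markers.** With equal baseline and post-treatment variances and baseline correlation r, the variance relative to comparing post-treatment values alone is 2(1−r) for change scores and 1−r² for baseline adjustment. For assumed r = 0.3 this is 1.40 against 0.91; for r = 0.6 it is 0.80 against 0.64. The article gives no value for r, so this shows direction and not a forecast.

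**The case against.** The strongest reply is that section 3.4 calls the simple tests preliminary and then plans additive models and risk-factor subgroups. History of preterm delivery, which the article itself ranks first, would be a natural term in both. A condensed article leaves covariates to the full protocol or analysis plan, and section 3.1 mentions a detailed protocol that is not shown. This stands to the extent that a reader may not infer that the simple tests are the final comparison, or that the stratum will be left out. The text does not settle either. What remains is that the article does name tests, that none of them matches its stratified design, and that it names no confirmatory test of treatment.

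A reader might also infer that the trial misses its 80% power because Fisher reaches only 77.3%. The article does not assign Fisher to the main outcome. With 45 and about 22 expected events (750·0.06 and 750·0.03) chi-square is adequate, and the sample size matches it.

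A third tempting reading is that baseline pH, Nugent score and cytokines are ignored. Section 3.1 plans to evaluate changes, and change uses the baseline. Nor does the article say that raw post-treatment values will be compared, so a precision gain measured against such a comparison would not describe this plan.

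**Conclusion.** The point holds as a modest improvement. The randomisation is stratified on a factor said to triple risk, the named tests are unstratified, and no sentence brings the stratum into the comparison of arms. At the article's threefold risk, using an unstratified chi-square test would cost about 0.3 to 0.4 points of power and make the test slightly conservative. It produces no bias and no excess false positives, power stays above 80%, and 1500 women remain enough. These figures rest on the assumed prevalence of 5% to 30%, two-sided testing, 1:1 allocation and a common relative effect. The open choice between chi-square and Fisher matters more (3.7 points), but only if Fisher were applied to the main outcome. For the secondary markers the gain from baseline adjustment is real in direction, and its size cannot be given from the document.

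**What to change.** State one primary analysis: the intention-to-treat comparison of spontaneous preterm delivery before 34 weeks by a Cochran-Mantel-Haenszel test stratified by history of preterm delivery, reported with the common risk ratio and its 95% confidence interval. A regression model with arm and stratum would serve equally. Reserve the Fisher test for sparse neonatal outcomes. If the additive models are meant to estimate the treatment effect, say so and list arm and stratum among their terms.

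For the secondary markers, compare arms after treatment with the baseline value and the stratum as covariates: an ordinal model for Nugent score and for pH, which is read in steps of 0.5, and analysis of covariance on log cytokines.

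The stratum is known for every randomised woman because it determined her list, and section 3.1's plan to evaluate change presupposes baseline marker values. The cost is therefore analysis wording alone, with no change to sample size or data collection. Section 3.6 says recruitment has finished, so the wording should be fixed before unblinding.

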### 3.5. Ethical issues

The trial was approved by an Institutional Review Board and by the National Review Board (CONEP). The trial will be monitored by an independent data monitoring committee.

The trial conduction will follow ICH/GCP Regulation and the local regulation for clinical trials.

### 3.6. Registration

The study has been registered at the NIH register platform; its identifier is NCT00303082. The study has recently finished recruiting patients.

Sponsors: The trial received grants from FIOCRUZ/Brazilian Health Ministry, SAS/Brazilian Health Ministry and Rio de Janeiro State Research Foundation.
